## **6.2 Study Materials**

Fondazione NIBIT will provide Case Report Forms.

## **6.3 Safety Assessments**

Data for the procedures and assessments specified in this protocol should be submitted to Fondazione NIBIT/CRO on a case report form. Additional procedures and assessments may be performed as part of standard of care; however, data for these assessments should remain in the subject's medical record and should not be provided to Fondazione NIBIT/CRO, unless specifically requested.

All subjects who receive at least 1 dose of study drug will be evaluable for safety parameters. Additionally, any occurrence of non-SAE or SAE from time of consent forward, up to and including follow-up visits, will be reported. See Section 7: Adverse Event Reporting.

The visits will occur on every treatment day and also on Day 8, for all cycles, on Day 8,15 for the first cycle. There is a 30-day (+ 5 day) safety visit after the last study treatment in this study.

Safety will be evaluated for all treated subjects using the NCI CTCAE version 4.0. Safety assessments will be based on medical review of AE reports and the results of vital sign measurements, physical examinations and clinical laboratory tests. The incidence of AEs will be tabulated and reviewed for potential significance and clinical importance.

Safety monitoring will be performed on an on-going basis as described in Section 4.1.3.

### ***6.3.1 Medical History, Physical Exam, Physical Measurements***

A detailed Medical History will be obtained at Screening. Medical history must include date of diagnosis, including histological or cytological documentation of malignancy. Any toxicity related to previous treatments should be mentioned, if applicable.

A complete physical examination including subject's height and weight will be performed at Screening. Prior to dosing (within 3 days), the subject's weight must be obtained to calculate the ipilimumab dose and the subject's body surface area on which SGI-110 dose is calculated.

If the Screening physical exam is conducted within 24 hours of dosing on Week 0, then a single examination may count as both Screening and Pre-dose examination. Subsequent physical exams will be performed if clinically indicated. Any physical examination finding that qualifies as an AE or SAE must be documented on the appropriate CRF pages. Pre-treatment events present within 2 weeks of starting therapy, whether or not related to current disease, will be captured prior to the study start. Any worsening ( $\geq 1$  Grade from Baseline) will be documented as an AE in the CRF.

### **6.3.2 Vital Signs**

Vital signs consist of blood pressure, heart rate, and temperature.

During ipilimumab infusions, vital sign measurements except body temperature must be performed prior to dosing, every 30 minutes for the duration of the infusion and 1 hour following completion of the infusion or until the patient is stable. Orthostatic (supine and standing) BP and heart rate are to be measured when clinically indicated (e.g., experiencing light-headedness, dizziness, syncope).

On-treatment clinically significant findings will be reported on the AE CRF.

### **6.3.3 Pregnancy Testing**

WOCBP are required to have several pregnancy tests performed. A negative serum pregnancy test must be documented at the Screening. Additionally WOCBP must exhibit a negative serum or urine pregnancy test (minimum sensitivity 25 IU/L or equivalent units of HCG) within 24 hours prior to the start of study drug, therefore the Screening pregnancy test may need to be repeated prior to the start of study drug dosing.

A pre-dosing urine pregnancy test must be performed prior to each ipilimumab dosing as outlined in Table 6.1.

### **6.3.4 ECOG Status**

ECOG performance status will be evaluated at the screening evaluation and at each visit as outlined in Table 6.1. If patient discontinues SGI-110 dosing but remains on ipilimumab, performance status will be reported prior to ipilimumab dosing only.

### **6.3.5 Adverse Events Monitoring**

Adverse Events (AEs) will be evaluated according to the NCI CTCAE Version 4.0 on a continuous basis starting from when the subject takes the first dose of study treatment, up to and including Follow-up visits (at minimum, for 70 days following last dosing).

Serious Adverse Events (SAEs) must be collected from the time period following written consent to participate in the study up to and including Follow-up visits (at minimum, for 70 days following last dosing).

### **6.3.6 Concomitant Medications**

Concomitant medications will be recorded in the concomitant medication log. Any changes to concomitant medications will be recorded at each visit.

Any systemic or local corticosteroid that is prescribed for treatment emergent or disease related medical conditions will be recorded on the concomitant medication log. The information on corticosteroids must include the name of the drug, dose, dosing frequency and any information relevant to the use of

corticosteroids used to treat irAEs or emergent neurological complications. Investigators should add any clinical notes about the response to corticosteroid therapy as it relates to clinical or radiologic status changes.

### **6.3.7 Laboratory Test Assessments**

#### **6.3.7.1 Serum Chemistry**

Serum Chemistry is to be obtained as outlined in Table 6.1. Serum chemistry tests are to include: albumin, amylase, lipase, BUN, creatinine, ALT, AST, LDH, serum alkaline phosphatase, direct and total bilirubin, glucose, total protein, sodium, potassium, chloride, HCO3, calcium, uric acid and TSH. Additional draws must be incorporated when monitoring recovery from any non-hematologic AE (e.g., elevations in ALT, AST).

Note: ALT, AST, and total bilirubin must be performed within 3 days of ipilimumab and SGI-110 dosing. The results of these tests must be reviewed by the principal investigator (or designee) prior to dose administration.

#### **6.3.7.2 Hematology**

A CBC with differential is to be obtained as outlined in Table 6.1. The CBC with differential is to include: hemoglobin, hematocrit, white blood cells, platelets (direct platelet count), WBC differential enumeration of total and percentage of neutrophils, lymphocytes, eosinophils, basophils and monocytes. Additional draws must be incorporated when monitoring recovery from any hematologic AE.

CBC with differential must be performed within 3 days prior to ipilimumab and SGI-110 dosing. Results must be reviewed by principal investigator (or designee) prior to dose administration.

#### **6.3.7.3 Urinalysis**

A urinalysis will be obtained prior to first dosing and will include a gross examination including: specific gravity, protein, glucose and blood. A microscopic evaluation will also be performed, as needed, to include WBC/HPF, RBC/HPF and any additional findings. This test could be repeated later during the course of the study if clinically indicated.

#### **6.3.7.4 HIV and Hepatitis Panel**

At screening as outlined in Table 6.1, testing should be performed for HIV antibody, hepatitis C antibody and HBsAg utilizing local standard informed consent procedures prior to this laboratory collection. These tests could be repeated later during the course of the study if clinically indicated.

### **6.3.8 Tumor Tissue biopsy**

Tumor tissue biopsy of cutaneous/subcutaneous lesions of at least 5 mm diameter will be performed for each subject at baseline, W4 and W12 as outlined in Table 6.1.

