**Supplementary Figure 1. NIBIT-M4 cohort.**

Overview of sample profiling and clinical information for N=14 patients of NIBIT-M4 trial.

[figure not shown]

**Supplementary Figure 2. Evaluation of the methylation pattern for lesions harboring mutation in chromatin organization (*DNMT1* or *SETD2*).**

**a** Global Methylation pattern as function of the time of biopsy in genomics regions for *DNMT1* and *SETD2* mutant and wild-type lesions. The increasing (green) or decreasing (red) trend was evaluated based on the inclination of the robust linear regression line between the three time points (mutant patients  $n=3$ , wild-type patients  $n=11$ ). **b** Regulatory regions (mutant patients  $n = 3$ , wild-type patients  $n = 11$ ). **c** Classes of long terminal repeat (LTR) (mutant patients  $n = 3$ , wild-type patients  $n = 11$ ). **d** Correlation between expression and methylation of LTR in mutant and wild-type cases (Spearman's correlation coefficient ( $r$ ) and associated  $p$ -values from two-tailed correlation test). Lines represent robust least squares linear regression. In **a**, **b**, **c**, and **d**, bands represent confidence intervals ( $\pm 0.95$ ) around a linear model fitted by robust regression using an M estimator. Source data are provided as a Source Data file.

[figure not shown][figure not shown]

**Supplementary Figure 3.** *Mutational signature analysis for patients with available matched normal.*

Deconvolution of the mutational patterns on COSMIC collection of mutational signatures v3.2. Source data are provided as a Source Data file.

a

[figure not shown]

b

[figure not shown]

c

[figure not shown]

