**a** Global Methylation pattern as function of the time of biopsy in genomics and regulatory regions for R (n = 18) and NR (n = 23) lesions. The increasing (green) or decreasing (red) trend was evaluated based on the inclination of the robust linear regression line between the three time points. Bands represent confidence intervals ( $\pm 0.95$ ) around a linear model fitted by robust regression using an M estimator. **b** Starburst plot of hyper-methylated and down-regulated genes (lower-left quadrant), and hypo-methylated and up-regulated genes (upper-right quadrant) between R (n = 6) and NR (n = 8) patients at different weeks of treatment (left). x and y axis represent the  $-\log(p\text{-value})$  multiplied by the sign of the difference from the differential methylation (from linear model, as implemented in the limma package) and expression analyses (from glmLRT, as implemented in EdgeR^12), respectively (left). Heatmap of enrichment scores as  $-\log_{10}(p\text{-value})$  from GO:BP over-representation analysis (as implemented in SMITE package) for hypo-methylated and up-regulated genes between R (n = 6) and NR (n = 8) patients at different weeks of treatment (right). Source data are provided as a Source Data file.

**a**

[figure not shown]

**b**

[figure not shown]

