### ***1.3.3 Immunomodulatory activity of SGI-110 in hematologic malignancies***

The immunomodulatory activity of SGI-110 has been investigated in AML and MDS patients enrolled in the dose escalation study segment of the first-in-human phase1/2 study NCT01261312. Bisulfite-modified blood DNA was analyzed by quantitative methylation-specific PCR for pre and post-treatment methylation on the promoters of CTA genes, NY-ESO-1 and MAGE-A1. The extent of demethylation of these genes was higher in patients treated with the Daily x5 schedule than in the weekly x3 schedule. A dose-dependent increase in post-treatment demethylation was observed in all the cohorts up to 125 mg/m^2; the most potent average gene promoter demethylation (14% for NY-ESO-1 and 16.3% for MAGE-A1) was observed in patients treated at 125 mg/m^2 Daily x5. Duration of gene promoter demethylation for NY-ESO-1 and MAGE-A1 was very similar to the duration observed for LINE-1 with a nadir on day 8 and an almost complete re-methylation by day 28. SGI-110-induced gene promoter demethylation resulted overall in the up-regulation or *de novo* induction of NY-ESO-1, MAGE-A1 and MAGE-A3 expression. Total RNA from blood of 23 patients treated with 36- 125 mg/m^2 SGI-110 Daily x5 was available for analysis; *de novo* induction or up-regulation of NY-ESO-1, MAGE-A1 or MAGE-A3 expression was observed respectively in 14, 7 and 11 patients. These changes in CTA expression are directly associated to a dose-dependent reduction of CTA promoter methylation, supporting a direct role of pharmacologic DNA demethylation in the observed modulation of the tumor immune profile.

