### ***5.2.1 Dosage and Administration***

#### ***SGI-110 schedule***

SGI-110 will be administered:

Start at 30 mg/m^2 day s.c. on W0, 3, 6, 9 Day 1 - 5 q21 days. Dose Level -1: 15 mg/m^2 day; dose level +1: 45 mg/m^2 day, Dose Level +2: 60 mg/m^2 day for a total of 4 cycles.

SGI-110 is administered by SC injection preferably in the abdominal area; however the thigh and arms may be used. A Luer-Lok disposable syringe should be used when dispensing and administering SGI-110. Due to the slightly viscous nature of the preparation, use of thin-walled subcutaneous needle is highly recommended for ease of subcutaneous administration and subject comfort. SGI-110 should be injected slowly (up to one minute) as some injection site discomfort or pain may be experienced.

If injection site pain is reported upon injection, apply ice packs to the injection site both before and after injection. If the injection site events are reported at subsequent injections despite slow injection and the use of ice packs, pre-treatment with topical or systemic analgesics can be considered. The total amount (in mg) of SGI-110 to be administered will be determined based on the body surface area (BSA). In calculating the BSA, actual heights and weights taken at enrolment should be used. There will be no adjustments to “ideal” body weight or dose modifications related to changes in body weight < +/- 10%. The institutional standard for calculating BSA is acceptable.

The site(s) of SGI-110 SC injections will be captured on the dosing CRF.

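### The Week 4 and Week 12 biopsies fall on cycle Day 8 and Day 22; one slope across them ignores or reverses the Week 4 effect and can strongly understate demethylation

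*Combined protocol and SAP*

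**What the plan says.** Section 6.3.8 states that tumour biopsy "will be performed for each subject at baseline, W4 and W12 as outlined in Table 6.1". Section 5.2.1 gives SGI-110 "s.c. on W0, 3, 6, 9 Day 1 - 5 q21 days", for four cycles.

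Section 1.3.3 reports how promoter methylation behaved under the five-day regimen in an earlier study: "with a nadir on day 8 and an almost complete re-methylation by day 28". It adds that LINE-1 followed a very similar course. The material was blood from AML and MDS patients: "Bisulfite-modified blood DNA was analyzed by quantitative methylation-specific PCR for pre and post-treatment methylation on the promoters of CTA genes".

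The trend method appears in the figure legends. Supplementary Figure 6a says: "The increasing (green) or decreasing (red) trend was evaluated based on the inclination of the robust linear regression line between the three time points". The bands are drawn "around a linear model fitted by robust regression using an M estimator", and the data are given "for R (n = 18) and NR (n = 23) lesions". Supplementary Figure 2a uses the same rule for mutant and wild-type cases.

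Appendix A names the tumour methylation assays but no longitudinal model, and neither it nor Section 6.3.8 mentions the cycle day of a biopsy. Section 8.3.3 makes the translational work exploratory, without formal tests.

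**The concern.** The two on-treatment biopsies are taken at different points of the dosing cycle. Week 4 is 7 days after a cycle start and Week 12 is 21 days after one. Counted from the last injection on Day 5, the gaps are about 3 and 17 days. A straight line in study time cannot separate the depth of demethylation from its recovery between doses.

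The middle point of three also has little or no influence on a fitted slope, and here the middle point is the biopsy nearest to the reported nadir. The sign of that slope then becomes the label. Appendix A intends to relate treatment-induced changes in tumour to clinical outcome, so a label that misses a real pharmacodynamic effect would weaken that reading.

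**Working it through.** The plan states no figure for this analysis, so there is none to reproduce.

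**1. Cycle days (Sections 5.2.1 and 6.3.8)**

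- Week 4: last cycle start is Week 3; (4 − 3) × 7 + 1 = Day 8 of Cycle 2.
- Week 12: last cycle start is Week 9; (12 − 9) × 7 + 1 = Day 22 of Cycle 4.

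**2. Weight of each biopsy in a least-squares slope**

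Time in weeks (0, 4, 12): the mean is 16/3 = 5.33, the deviations are −5.33, −1.33 and +6.67, and their squares sum to 74.67.

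Slope = (−5.33·y0 − 1.33·y4 + 6.67·y12) / 74.67

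Week 4 has a negative weight: for a fixed Week 12 value, lower methylation at Week 4 makes the slope more positive.

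Equally spaced times (0, 1, 2): slope = (y12 − y0) / 2. Week 4 drops out.

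This step needs no assumption about kinetics. It needs near-balanced data. With 6 responders and 8 non-responders (Supplementary Figure 6b), 18 = 6 × 3 and 23 = 8 × 3 − 1, which is nearly balanced.

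**3. Size**

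Let D be the fall at Week 4 and r the share of it still present at Week 12, so that y = (0, −D, −rD).

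- Weeks: slope = D(1.33 − 6.67r)/74.67 = D(0.0179 − 0.0893r) per week. It is zero at r = 0.20, positive below that and negative above.
- Equal spacing: slope = −0.5rD per step, never positive in expectation.
- Benchmark, sustained effect (r = 1): −0.0714D per week, or −0.5D per step.

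**4. Range for r (assumption)**

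No Day 22 value is given. Let q be the share of the effect left at Day 28. From Day 8 to Day 22 is 14 of the 20 days to Day 28. Linear recovery gives r = 1 − 0.7(1 − q); exponential recovery gives r = q^0.7.

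| Recovery | q | r | Slope per week | Share of sustained slope, weeks | Same, equal spacing |
|---|---|---|---|---|---|
| Linear | 0 | 0.30 | −0.0089D | 12.5% | 30% |
| Linear | 0.10 | 0.37 | −0.0152D | 21% | 37% |
| Exponential | 0.10 | 0.20 | 0 | flat | 20% |
| Exponential | 0.05 | 0.12 | +0.007D | rising | 12% |

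Letting residual effect from earlier cycles add up under the exponential form leaves the ratio of the Week 12 to the Week 4 effect at 0.20 and 0.12.

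At r = 0.30 the line in weeks shows a change of 12 × (−0.0089D) = −0.11D over the study. The direct Week 12 minus baseline difference is −0.30D, and the Week 4 difference is −D.

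**5. Robust fit**

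The legends use an M-estimator, so the slope was also simulated with a Huber fit: 6, 8 or 14 patients at three times, independent normal errors with assumed SD 0.5D or 1.0D, 600 runs per setting.

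| Time coding | r | Share of runs with a positive slope |
|---|---|---|
| Weeks | 0.20 | 0.46–0.52 |
| Weeks | 0.30 | 0.30–0.42 |
| Weeks | 0.37 | 0.18–0.41 |
| Weeks | 1 | 0–0.07 |
| Equal spacing | 0.30 | 0.04–0.31 |

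The value near one half at r = 0.20 agrees with the least-squares crossing point.

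**The case against.** **The kinetics may not transfer.** They come from blood of AML/MDS patients; the documents give none for melanoma tissue. The ±3 day treatment-phase window also lets Week 4 fall anywhere from Day 5 to Day 11. This stands. A reader might infer that the tumour is sampled at its nadir, but the documents support only that Week 4 falls on the day reported as the nadir in blood.

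**Reversal is the extreme case.** A reader might infer that true demethylation will be reported as no effect or as a rise. In expectation that needs r of 0.20 or less with time in weeks; linear recovery leaves 0.30 to 0.37. The legends do not state the time coding, and with equal spacing a positive slope comes only from noise or overshoot. Attenuation is the supportable claim.

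**The slope is not in the protocol text.** It appears only in legends that report results, and it is not the only analysis: Supplementary Figure 6b compares the response groups at separate weeks, and Supplementary Figure 7 contrasts Week 12 with Week 0. True, but these do not correct the trend label, and the gap in Appendix A is what leaves the choice open.

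**Responders and non-responders share one schedule.** A reader might suspect that timing creates a difference between them. Unequal cycle phase does not do so by itself.

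**Blood LINE-1.** Week 1 and Week 4 samples fall on Day 8, and Week 3 and Week 12 on Day 22, but no line is specified for that series, so the point does not extend to it.

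**Conclusion.** The point holds as an improvement to an exploratory analysis. Two parts rest on the documents and arithmetic alone: the cycle days are 8 and 22, and a least-squares line gives Week 4 a negative weight (weeks) or zero weight (equal spacing). The size rests on carrying blood kinetics over to tumour and on an assumed recovery shape. With linear recovery and 0 to 10% left at Day 28, the slope in weeks is 12.5% to 21% of the sustained-effect slope; with equal spacing it is 30% to 37%. An expected slope that is flat or rising requires time in weeks and 20% or less of the effect remaining at Week 12. The primary endpoint is untouched, and nothing here shows that any published trend label is wrong.

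**What to change.** In Appendix A, specify two paired within-patient contrasts for tumour methylation: Week 4 minus baseline and Week 12 minus baseline. Report them separately, each with the actual cycle day of the biopsy. Use them in place of the single slope and its increasing/decreasing label in the trend panels.

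Do not add days since dose as a covariate: on a fixed schedule it is nearly collinear with visit and it is undefined at baseline. The planned blood LINE-1 work needs no change on this account.

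No further biopsies are needed. Section 5.5 already has drug administration recorded in the CRF, so cycle day follows from the biopsy date. The cost is two estimates in place of one in a small sample (14 patients in the figures), each with limited precision.

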## **6.4 Efficacy Assessments**

Data for the procedures and assessments specified in this protocol should be submitted to Fondazione NIBIT/CRO on a case report form. Additional procedures and assessments may be performed as part of standard of care; however, data for these assessments should remain in the subject's medical record and should not be provided to Fondazione NIBIT/CRO, unless specifically requested from the sponsor.

### **6.4.1 Primary Efficacy Assessment**

The primary endpoint of this study is safety, tolerability, and Maximum Tolerated Dose (MTD) of SGI-110 in combination with ipilimumab in 21 day cycles in melanoma patients. Every effort should be made to collect, all safety data.

### **6.4.2 Secondary Efficacy Assessment**

- To evaluate the immune-related (ir) -Disease Control Rate (ir-DCR), immune-related (ir) -Objective Response Rate (ir-ORR), immune-related (ir) -Time to Response (ir-TTR) and immune-related (ir) -Duration of Response (ir-DOR),
- To evaluate median immune-related (ir) Progression Free Survival (ir-PFS), median Overall Survival (OS), and survival rate at 1 and 2-years.

### **6.4.3 Exploratory Assessment**

- To investigate immune-biologic correlates to treatment with SGI-110 in combination with ipilimumab (see Appendix A),
- Characterize pharmacokinetic profile of SGI-110 and decitabine. For a detailed workplan of pharmacokinetic analyses see Appendix B.

#### **6.4.3.1 Radiologic Assessment of Tumor Lesions**

CT scans with IV contrast and oral contrast of brain, neck, chest, abdomen, pelvis and  $\pm$  soft tissue (or MRI, if iodine contrast media is medically contra-indicated) have to be performed for ALL patients at all Screening and at each tumor assessment visit. CT/MRI scans must be obtained of anatomic regions not covered by the chest, abdomen and pelvic scans, in subjects where there is clinical suspicion of deep soft tissues metastases (e.g., lesions in the thigh). Such additional CT/MRI scans will be required at Screening

only when deep soft tissue disease is known or suspected and must be consistently repeated at all tumor assessment visits if a deep soft tissue lesion is identified.

Similar methods of tumor assessment and similar techniques must be used to characterize each identified and reported lesion at Screening during the Treatment and Follow-up Phases. Response or progression of disease must be documented by a CT or an MRI similar to the methods used at Screening.

A reference measurement ruler must be printed on every image for scale determination. Sections should be contiguous, similarly sized and consistent from visit-to-visit. Section thickness must be based on institutional standards (e.g., from 5 to 8 mm, 10 mm cuts are not recommended). Chest x-rays and ultrasound are not acceptable methods to measure disease. Response or progression of disease must be documented by a CT or an MRI similar to the methods used at Screening.

